### 8.6.2 Protocol Deviations

Protocol deviations are defined as instances where protocol requirements are not followed in such a manner whereby data is unusable or unavailable. Protocol deviations are less serious in nature and do not require IRB/IEC notification, as long as they do not have an effect on the rights, safety or welfare of the study subjects.

Protocol deviations include, but are not limited to:

- Procedure not performed within the allowed follow-up window
- Required data not obtained
- Follow-up procedure performed at an unapproved location

The study site should report the protocol deviation on the applicable eCRF.

## 8.7 Audits / Inspections

Study centers may be audited during the course of and after completion of the clinical investigation by BIOTRONIK or BIOTRONIK designees, IRB/IEC, competent authority or other applicable regulatory authorities.

The investigator must provide the auditor with all clinical investigation documents including the medical records for all enrolled subjects.

BIOTRONIK will evaluate any non-compliance and issue corrective actions, discontinue enrolment or at last measure, close the clinical investigation site, if monitoring or auditing identifies serious or repeated deviations on the part of an investigator.

## 9. REGULATORY REQUIREMENTS

### 9.1 Compliance Statement

This clinical investigation will be contributed in compliance with the applicable regulations for conduction of clinical investigations with human beings, especially with regard to:

- The Declaration of Helsinki current version (Fortaleza version 2013, active at protocol signature)
- ISO 14155 current version (version 2011, active at protocol signature) Clinical investigation of medical devices for human subjects - Good clinical practice
- Medical Device Directive 93/42/EEC
- ICH/GCP current version (version 2002, active at protocol signature)
- All applicable local and national requirements in the participating countries (including safety reporting, e.g. "Verfahren schwerwiegende unerwünschte Ereignisse in Deutschland" dated 06Dec2019 and "Safety reporting procedures Switzerland" dated 10Jan2020).

### 9.2 IRB/IEC and Regulatory Bodies

The clinical investigation plan as well as other relevant study documents required will be submitted for approval by the IRB/IEC and competent authority prior to study start as required by local and national regulations.

BIOTRONIK will record changes to the clinical investigation plan in the revision history. Amendments will be submitted to the involved IRB/IEC and respective competent authorities as applicable according to national or local regulations. All study personnel will be trained on all amendments as required.

All subjects must be provided with a written informed consent form which is approved by the site's IRB/IEC. Each site must provide BIOTRONIK AG with a copy of the clinical site's IEC/IRB approval letter or vote and the IRB/IEC approved informed consent. In addition the composition of the IRB/IEC and a statement about compliance to GCP is required. Approvals for the continuation of the trial at each clinical site must be kept current and notifications forwarded to BIOTRONIK.

### **9.3 Insurance**

Subjects who participate in this study will be insured for study related injury according to local regulatory requirements. BIOTRONIK will organize appropriate insurance coverage which will be available throughout the entire study.

### **9.4 Subject data protection**

Subject's protection of personal data will be maintained throughout the study. It has to be ensured that all data collected can be tracked back to the source data, if required. For this purpose, a unique subject identification code (i.e. subject number) will be used that allows identification of all data reported for each subject.

Data relating to the study might be made available to third parties (e.g. in case of an audit performed by regulatory authorities) preconditioned the data are treated confidentially and that each subject's privacy is guaranteed.

### **9.5 Records**

Records to be maintained by the investigator include, but are not limited to:

- Clinical trial investigational plan and all amendments
- Investigators Brochure and amendments
- Contact list sponsor/study site
- Signed clinical trial agreement

- IRB/IEC correspondence, approval letter, including informed consent
- IRB/IEC membership list
- Regulatory authority notification, correspondence and approval
- Insurance certificate
- If applicable, device shipping records, device accountability
- Correspondence relating to the trial
- CVs for all investigators and key members of the investigation site team
- Training records
- Financial Disclosure Forms for all investigators
- Site personnel signature list and delegation of authority form
- Monitoring visit log
- Blank set of CRFs and instructions for completion
- Subjects screening/enrollment log
- Subjects identification log
- Lab certification and lab test normal ranges
- Adverse event forms
- Reports (including interim reports, final reports and safety reports)

BIOTRONIK will retain relevant study documentation in the Trial Master File (TMF) according to international legislation and BIOTRONIK Standard Operating Procedure (SOPs).

## 9.6 Record Retention

All study records and reports will remain on file at the sites for a minimum of 10 years after completion of the trial and will further be retained in accordance with local and international guidelines as identified in the clinical study agreement.

The investigator must contact BIOTRONIK before destruction of any records and reports related to the clinical investigation. BIOTRONIK must be informed if the investigator plans to leave the clinical investigation site. In such case the site must

name a new contact person before the investigator parts from the clinical investigation site.

## 9.7 Study Termination

BIOTRONIK will monitor the progression of the clinical investigation. If warranted, the clinical investigation may be suspended or discontinued early if there is an observation of serious adverse reactions presenting an unreasonable risk to the clinical investigation population.

The following stopping rules were set up by the data safety monitoring board. As the enrolment duration is planned for up to 5 months, only events during the first 30 days of each patient's individual follow-up time will be considered for the stopping rules.

In general, the monitoring method expressed in the stopping rules are based on the application of the sequential ratio probability test (126). For the different event types a postulated value, an upper limit, a fixed alpha error of 5% and a beta error of 20% were used. If the number of events is equal or higher than the numbers of events in the left column of the tables at the moment when the number of patients in the right column is recruited, a DSMB meeting will be held in order for the members to review and to vote whether a potential suspension of patient enrolment must be considered.

Cardiac death, target vessel related MI, and scaffold thrombosis are relevant for patient's safety. All events are rare. In the comparable BIOSOLVE II and BIOSOLVE III (studies testing the Magmaris device, see also section 1.1.3), one patient was affected by these events.

Using the point estimator of 0.8% (BIOSOLVE III 30 days event rate of the combination cardiac death, target vessel related MI, and scaffold thrombosis) as the postulated value, and 4.6% (BIOSOLVE III upper 95% confidence limit for estimation of combined event rate) as an upper limit, the resulting stopping rules are as follows:

| Number of event | Patients included |
|-----------------|-------------------|
| 2               | 20                |
| 3               | 66                |
| 4               | 112               |

In addition, the 30 days event rate of clinical driven TLR should be monitored. Using 0.1% as postulated value (BIOSOLVE III no event) and 4.6% as an upper limit, the resulting stopping rules are as follows:

| Number of event | Patients included |
|-----------------|-------------------|
| 1               | 23                |
| 2               | 107               |

BIOTRONIK may also terminate investigator and site participation in the clinical investigation if there is evidence of failure to maintain adequate clinical standards, failure to comply with the clinical investigational plan, fraud or any other forms of misconduct.

In the event of clinical investigation termination or suspension, BIOTRONIK will send a report outlining the circumstances to the corresponding IRB/IEC, regulatory body and all investigators. A suspended or terminated clinical investigation may not be re-initiated without approval of the corresponding IRB/IEC and competent authority.

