#### 4.6 Study Duration

The anticipated duration of this clinical investigation is approximately 3.5 years (First Subject In until Last Subject Out):

Enrolment duration: approximately 15 months

Follow up phase: 3 years

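### The stopping boundaries in section 9.7 are read at recruitment of the nth patient but were derived for n complete 30-day outcomes, which weakens mainly the first boundaries

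*Protocol*

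**What the plan says.** Section 9.7 sets two boundary tables, each pairing a number of events with a number of patients: 2/20, 3/66 and 4/112 for the composite of cardiac death, target vessel MI and scaffold thrombosis, and 1/23 and 2/107 for clinically driven target lesion revascularization (TLR).

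- **Numerator.** Only events in the first 30 days of a patient's "individual follow-up time will be considered for the stopping rules".
- **Time of reading.** The count is compared with the table "at the moment when the number of patients in the right column is recruited". The right column is headed by patients included. No patient is required to have reached day 30, and no later re-reading is set.
- **Design.** A sequential probability ratio test, for which "a fixed alpha error of 5% and a beta error of 20% were used". For the composite: "Using the point estimator of 0.8"% as the postulated value and "4.6% (BIOSOLVE III upper 95% confidence limit for estimation of combined event rate) as an upper limit". For TLR: "Using 0.1% as postulated value (BIOSOLVE III no event) and 4.6% as an upper limit".
- **Consequence.** Reaching a boundary convenes the DSMB, which votes on whether suspension of enrolment must be considered.
- **Accrual.** Section 9.7 bases the 30-day restriction on an enrolment of at most five months. Section 4.6 states "Enrolment duration: approximately 15 months", as does the synopsis.

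**The concern.** A patient recruited on the day a boundary is read adds one to the denominator while none of that patient's 30 days has been observed. Those recruited in the preceding month contribute only part of theirs. If one of the first 20 patients has an event after patient 20 is recruited, the 2/20 reading has passed and the event can count only towards 3/66. The error always runs towards missing a signal and is largest at the earliest boundaries, on which a first-in-man study relies to notice an unsafe device early.

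**Working it through.** **1. Reproduce the tables.** Inputs from section 9.7: α = 0.05, β = 0.20; p0 = 0.008 and p1 = 0.046 (composite); p0 = 0.001 and p1 = 0.046 (TLR). The upper boundary of the sequential probability ratio test for d events is

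n(d) = d + [d·ln(p1/p0) − ln((1−β)/α)] / ln((1−p0)/(1−p1)), rounded down, with ln(0.80/0.05) = ln 16 = 2.773.

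- Composite: ln(0.046/0.008) = 1.749 and ln(0.992/0.954) = 0.03906. n(2) = 2 + (3.498 − 2.773)/0.03906 = 20.58; n(3) = 66.37; n(4) = 112.15. Printed: 20, 66, 112.
- TLR: ln(0.046/0.001) = 3.829 and ln(0.999/0.954) = 0.04609. n(1) = 1 + (3.829 − 2.773)/0.04609 = 23.91; n(2) = 107.98. Printed: 23, 107.

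All five agree. The formula treats each of the n patients as a known yes or no at 30 days.

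**2. Error rates with complete outcomes.** These come from an exact recursion over up to 115 patients.

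- Composite: power 0.796, so beta 0.204; alpha 0.030. The first boundary alone: 1 − 0.954^20 − 20 × 0.046 × 0.954^19 = 0.234.
- TLR: power 0.967, so beta 0.033; alpha 0.026. The first boundary alone: 1 − 0.954^23 = 0.661.

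The composite design meets its stated 20% beta when read this way.

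**3. How much follow-up is missing.** Assume 115 patients accrue evenly and that recruitment and procedure fall on the same day.

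- 15 months: 115/(15 × 30.44) × 30 = 7.6 patients per 30 days. When patient 20 is recruited, about 20 − 7.6 = 12 have 30 days observed.
- 5 months: 115/(5 × 30.44) × 30 = 22.7 patients per 30 days. When patient 20 is recruited, none has.

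**4. Error rates as worded.** The protocol does not give the timing of events within 30 days. The share on day 0 was therefore varied, with the rest spread evenly over 30 days. Simulation of 100,000 trials per row, true rate 4.6%:

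| Enrolment | Events on day 0 | 2/20 met | Composite beta | 1/23 met | TLR beta |
|---|---|---|---|---|---|
| Complete data | – | 23.4% | 0.204 | 66.1% | 0.033 |
| 15 months | 0% | 16.1% | 0.233 | 58.5% | 0.040 |
| 15 months | 50% | 19.6% | 0.219 | 62.3% | 0.037 |
| 15 months | 80% | 22.0% | 0.210 | 64.7% | 0.034 |
| 15 months | 100% | 23.5% | 0.203 | 66.3% | 0.032 |
| 5 months | 0% | 5.5% | 0.291 | 40.9% | 0.057 |
| 5 months | 50% | 13.6% | 0.245 | 54.9% | 0.043 |
| 5 months | 80% | 19.5% | 0.220 | 62.0% | 0.037 |
| 5 months | 100% | 23.7% | 0.203 | 66.2% | 0.033 |

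The 100% rows match complete data within simulation error. Random (Poisson) arrivals shift the results by about one percentage point. With no events on day 0 and 15 months, 2/20 is met 15.5% of the time and composite power is 76.3% (beta 0.237); at 5 months power is 70.0% (beta 0.30).

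**5. Two ways of repairing the denominator.**

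- The first n consecutive patients, each followed to 30 days: composite power about 0.80, alpha about 0.03, as in step 2.
- Patients who have either completed 30 days or had an event: event patients enter at once while event-free patients wait a month, so the observed proportion is biased upwards. In simulation, composite alpha rose to as much as 5.9% at 5-month accrual, above the stated 5%.

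**The case against.** A reader might infer that the stated 20% beta is simply not met. The documents do not support that in general.

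- For TLR it is wrong: overall beta is about 3–6% in every scenario.
- For the composite it depends on when events occur, which the protocol does not say. Should all of them be procedural, nothing is lost. With the 15 months of section 4.6 the rise is about 0 to 3 points.
- The starkest figures rest on the five-month enrolment printed in 9.7, which conflicts with the rest of the protocol and is a separate inconsistency.
- Beta belongs to the whole sequence. Even with complete data 2/20 is met only 23% of the time at 4.6%, and part of what is lost there is recovered at 3/66 and 4/112.
- Reaching a boundary convenes a meeting and does not stop the trial. The DSMB also assesses safety at intervals (section 8.1.1), and serious events go to the sponsor without unjustified delay (section 6.1).

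All of this stands, and it limits the size of the problem. It does not remove the mismatch: the wording and the calculation describe two different rules, and the worded one is the less sensitive unless every event falls on day 0.

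**Conclusion.** The point holds as a mismatch between how the boundaries were calculated and how section 9.7 says to read them. Its main effect is on early detection. At a true rate of 4.6%, the chance of meeting 2/20 falls from 23% to about 15–22% (15 months) or 6–20% (5 months), and the chance of meeting 1/23 falls from 66% to about 58% or 40% at worst. Overall composite beta moves from 0.204 to about 0.21–0.24 or 0.22–0.29. The composite ranges assume even accrual of 115 patients and 0–80% of events on day 0.

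The drop at 2/20 should not be read as a failure of the stated beta, and no failure can be claimed for the TLR rule. This is a modest correction that should be made, because the loss falls on the earliest looks of a first-in-man study.

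**What to change.** In section 9.7 and the DSMB charter:

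1. Define the right column as the first n consecutively treated patients.
2. Count every qualifying event in their first 30 days whenever it becomes known, and convene the DSMB as soon as the count is reached.
3. Close the reading for that n only when all n have a known 30-day outcome.
4. Reconcile the five-month enrolment premise in 9.7 with the 15 months in the synopsis and section 4.6.

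The printed boundaries can stay, with composite power about 0.80 and alpha about 0.03. Any crossing that the present wording would catch is still caught, and no sooner reading is given up. Do not define the denominator as patients who have completed 30 days or had an event, for the reason in step 5 of the working.

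The cost is wording only, since the one-month visit already collects the data. The downside is that each boundary closes up to about a month later, so the 107 and 112 boundaries close when enrolment of 115 is essentially over. As worded, the 112 boundary already precedes only three further patients.

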### BIOSOLVE-III

The BIOSOLVE-III study is a prospective, multicenter study conducted in 61 subjects enrolled at 8 investigational sites. Clinical follow-up visits take place at 1, 6, and 12 months and annually until 3 years post-procedure, with an angiographic follow-up at 12 months. Primary endpoint is in-hospital procedural success.

BIOSOLVE-II and BIOSOLVE-III considered together have enrolled 184 patients. BIOSOLVE-II and III pooled data at 6 month follow-up showed 3.3% TLF rate, consisting of two cardiac deaths (1.1%), one target vessel myocardial infarction (0.6%), and three clinically driven TLR (1.7%) (19). In BIOSOLVE-III, there were significantly more type B2/C lesions than in BIOSOLVE-II (80.3% vs 43.4%,  $P<0.0001$ ) and significantly more moderate-to-severe calcifications (24.2% vs 10.7%,  $P=0.014$ ). In spite of that, the clinical event rates remained stable. There was no definite or probable scaffold thrombosis (21).

At 12 months, there was no difference in LLL between BIOSOLVE-II and BIOSOLVE-III (21). In the overall population, it was  $0.25\pm0.31$  mm in-segment and  $0.39\pm0.34$  mm in-scaffold. No additional TLF occurred between 6 and 12 months and no definite or probable scaffold thrombosis was observed.

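### The 0.8% and 4.6% behind the stopping rules cannot come from BIOSOLVE III as stated, and read literally the rule is checked late and on recruited rather than followed patients

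*Protocol*

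**What the plan says.** Section 9.7 of the protocol (Study Termination) says the stopping rules are "based on the application of the sequential ratio probability test (126"), and that for each event type "a fixed alpha error of 5% and a beta error of 20% were used", together with a postulated value and an upper limit.

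For the composite of cardiac death, target vessel MI and scaffold thrombosis it takes the postulated value "Using the point estimator of 0.8% (BIOSOLVE III 30 days event rate of the combination cardiac death" and the other two components), and for the alternative "4.6% (BIOSOLVE III upper 95% confidence limit for estimation of combined event rate) as an upper limit". The sentence just before refers to BIOSOLVE II and BIOSOLVE III together and says that "one patient was affected by these events". The resulting table is 2 events/20 patients, 3/66, 4/112.

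For clinically driven TLR it proceeds "Using 0.1% as postulated value (BIOSOLVE III no event) and 4.6% as an upper limit". That table is 1/23, 2/107.

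The event count is compared with the table "at the moment when the number of patients in the right column is recruited". Only events in each patient's first 30 days count. A crossing leads to a DSMB meeting and a vote on suspending enrolment, not to an automatic stop.

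Section 1.1.3 describes BIOSOLVE-III as "conducted in 61 subjects enrolled at 8 investigational sites". It gives BIOSOLVE-II 123 enrolled subjects and the two studies together 184.

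**The concern.** A study of 61 subjects cannot show an event rate of 0.8%. Two adjacent sentences in section 9.7 point to different bases: one event across both studies, and a rate credited to the smaller one alone. The numbers themselves suggest a third basis, BIOSOLVE-II. A reader cannot tell which experience the DSMB's thresholds were meant to reflect, and the choice moves them.

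Three related points sit in the same section:

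- The TLR rule reuses 4.6%, the composite's figure, without saying why.
- The method is sequential, but taken at its word the rule is applied only when 20, 66 or 112 patients (23 or 107 for TLR) have been recruited.
- It counts patients recruited, although the events are 30-day events, so recent recruits enter the denominator before their risk period is over.

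These thresholds decide when the DSMB meets to consider suspending enrolment in a first-in-man trial of up to 115 subjects. Their source and their timing should both be unambiguous.

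**Working it through.** **Inputs.** α = 0.05, β = 0.20; composite p0 = 0.008, p1 = 0.046; TLR p0 = 0.001, p1 = 0.046 (all section 9.7). Study sizes 61, 123 and 184 (section 1.1.3). Maximum enrolment 115 (section 4.4).

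**1. Reproduce the printed tables.** The sequential probability ratio test triggers at d events among n patients when

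d·ln(p1/p0) + (n − d)·ln[(1 − p1)/(1 − p0)] ≥ ln[(1 − β)/α],

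so the largest n for a given d is

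n = d + {d·ln(p1/p0) − ln[(1 − β)/α]} / {−ln[(1 − p1)/(1 − p0)]}, rounded down.

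- Common term: ln(0.80/0.05) = 2.7726.
- Composite: ln(0.046/0.008) = 1.7492; −ln(0.954/0.992) = 0.03906. For d = 2: 2 + (3.4984 − 2.7726)/0.03906 = 20.58. Likewise d = 3 gives 66.37 and d = 4 gives 112.15. Rounded down: 20, 66, 112.
- TLR: ln(46) = 3.8286; −ln(0.954/0.999) = 0.04609. For d = 1: 1 + (3.8286 − 2.7726)/0.04609 = 23.91; d = 2 gives 107.98. Rounded down: 23, 107.

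All five printed boundaries are reproduced.

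**2. Test the stated source.** With any denominator up to 61, the smallest non-zero rate is at least 1/61 = 1.64%. The table shows one event in each candidate denominator, the exact (Clopper-Pearson) two-sided upper limit, and the composite boundaries obtained by putting that pair into the formula above.

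| Basis | Rate | Upper limit | Boundaries within 115 patients |
|---|---|---|---|
| Printed | 0.8% | 4.6% | 2/20, 3/66, 4/112 |
| BIOSOLVE-III, 1/61 | 1.64% | 8.80% | 2/9, 3/33, 4/56, 5/79, 6/102 |
| BIOSOLVE-II, 1/123 | 0.81% | 4.45% | 2/18, 3/65, 4/111 |
| Pooled, 1/184 | 0.54% | 2.99% | 2/27, 3/97 |

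Denominators of 118 to 120 give 0.83% to 0.85% with upper limits of 4.56% to 4.63%, which round to the printed pair. The 1/61 row assumes one event in BIOSOLVE-III. Its boundaries are harder to cross than the printed ones; the pooled ones are easier to cross. At a true rate of 3% the chance of a trigger by patient 115 is 49.3% with the printed table, 48.3% with the 1/123 table and 57.7% with the two pooled rows shown.

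**3. The TLR limit.** The two-sided zero-event upper limit is 1 − 0.025^(1/N): 5.87% for 61, 2.95% for 123 and 1.98% for 184. The one-sided 95% limit for 61 is 1 − 0.05^(1/61) = 4.79%. None equals 4.6%. With p0 kept at 0.1%, 5.87% gives 1/22 and 2/92, and 4.79% gives 1/23 and 2/105. The 2.95% limit gives 1/22, with a second row (139.95) beyond the 115 maximum.

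**4. The reading rule.** An exact binomial recursion over 115 patients compares the printed composite table read only at 20, 66 and 112 with the same table read after every patient. It assumes each outcome is known at recruitment.

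| True rate | Trigger probability (either reading) | Listed counts only | After every patient |
|---|---|---|---|
| 0.8% | 2.95% | – | – |
| 4.6% | 79.6% | mean patient 63 | mean patient 48 |
| 8% | 98.5% | median patient 66 | median patient 24 |

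The means and medians are over runs that trigger. The median of 66 at 8% is partly an effect of having only three looks. The chance of a trigger at the first look is 1 − 0.92^20 − 20 × 0.08 × 0.92^19 = 48.3%, just under half. The mean at 4.6% describes the delay more steadily. As a concrete case, two events among the first five patients would formally wait until patient 20.

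**The case against.** The strongest reply is that only a study label is wrong. The boundaries follow from the printed rates, the probable source is BIOSOLVE-II, and with 1/123 the table barely moves. Most of this stands. It remains an inference, because the protocol gives no 30-day denominators and does not say which study the affected patient was in. Only the sponsor can settle it.

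A reader might infer that the boundaries themselves were miscalculated. Step 1 rules that out. A reader might also take the pooled 1/184 table as the correct replacement. The text does not say that the pooled count was the planning rate; it calls the inputs a postulated value and an upper limit, and says the DSMB set up the rules. Choosing among bases is therefore the DSMB's decision.

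On TLR, the protocol never presents 4.6% as a zero-event confidence limit, so failing to match one is not an error. What stands is that the figure has no stated basis.

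On the reading rule, events only accumulate, so an earlier crossing is still caught at the next listed count. The DSMB also reviews safety at intervals (section 8.1.1), and serious events are reported without unjustified delay (section 6.1), so the rule is not the only safeguard. A reader who inferred that fixed looks lose detection would be wrong under the assumption in step 4. The delay on the literal reading stands.

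**Conclusion.** The point holds in a limited form. Section 9.7 credits 0.8% and 4.6% to a study that cannot yield them, and it conflicts with section 1.1.3 and sits awkwardly with its own preceding sentence. Depending on which basis was meant, the first composite boundary falls at 9, 18 or 27 patients against the printed 20, and the second at 33, 65 or 97 against 66. If BIOSOLVE-II was meant, the practical effect is negligible and only the label needs correcting.

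The TLR limit is an unjustified input, not a demonstrated miscalculation. The literal reading rule postpones the DSMB meeting by about 15 patients on average at a true rate of 4.6% (63 − 48) and leaves the trigger probability unchanged. That equality assumes outcomes are known at recruitment. The effect of counting recruits who have not completed 30 days depends on recruitment speed and was not quantified.

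The results rest on one composite event in each candidate denominator, enrolled rather than 30-day denominators, and exact two-sided limits unless stated. A trigger calls a meeting, so none of this shows that the trial would have stopped or continued wrongly.

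**What to change.** - Reconcile section 9.7 with section 1.1.3 by naming the source study, the event count and the 30-day denominator behind 0.8% and 4.6%.
- Have the DSMB confirm both tables or recompute them from that source, and state the basis of the 4.6% used for TLR. The alternative boundaries above illustrate how far the tables could move; they are not proposed replacements.
- Reword the reading rule so that a DSMB meeting is called as soon as the event count reaches d while no more than n subjects have completed 30 days or had an event.

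The cost is one recalculation, a few sentences in section 9.7 and DSMB sign-off. Reading the printed table continuously does not raise the chance of a trigger under the assumption in step 4; it only brings the meeting forward.
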